### Data and statistical analysis

The primary analysis of the data will be undertaken using the principle of intention-to-treat (ITT). Our ITT analysis will include all participants including those who have missing data and those who are not fully compliant with the protocol. Some attrition is anticipated despite the fact that we will implement procedures to minimise loss to follow-up and participant withdrawal, and maximise adherence. Multiple imputation methodology will be employed to account for missing data [46].

Demographic and clinical characteristics as well as baseline data will be presented to assess the baseline comparability of the intervention groups. These variables will also be examined for those participants who withdraw from the study and those who remain.

Descriptive statistics will be presented for each group as the mean change (standard deviation, 95% confidence intervals) in the outcomes from baseline to each time point. Differences in mean change from baseline to each time point will be compared between groups using generalised linear regression modelling adjusting for baseline levels of the outcome measure. Model assumptions will be checked by standard diagnostic plots.

Improvement between active and sham physiotherapy groups based on the perceived ratings of change will be compared using log binomial regression and presented as relative risks with 95% confidence intervals.

As part of the secondary analyses of the primary outcomes at 13 and 36 weeks, we plan to conduct a separate analysis to estimate the effect of treatment in the hypothetical scenario of full adherence to randomised treatment modality. Adherence will be defined as attendance at more than 80% of scheduled treatment sessions and 60% of prescribed home exercise sessions in the active physiotherapy group. This is based on definitions used in another study of manual therapy and exercise in hip OA [47]. Analytical methods for this will utilise instrumental variables methodology involving two stage least squares estimation [48].

An index (with bootstrap 95% confidence intervals) to assess the success of participant blinding will be computed [49].

No statistical adjustment will be made for multiple testing. All tests will be two sided and carried out at the 5% level of significance. Any changes to the study design or analysis plan will be documented with full justification.

### Economic evaluation

The economic evaluation will be conducted from the perspective of the Australian health care system and the individual patient. The primary economic evaluation will take the form of a cost effectiveness study of the cost per extra quality adjusted life years (QALYs). QALYs will be calculated using the AQoL scores over 36 weeks. Differences in mean change from baseline for the AQoL to each time point will be weighted by the time from baseline using generalised linear regression modelling adjusting for baseline levels of the AQoL to construct QALYs, and then compared between groups. Differences in the mean cost between groups will be calculated using generalised linear regression modelling. Incremental cost per QALY will be calculated as the ratio of the difference in mean cost to the difference in mean QALYs with 95% confidence intervals calculated using Fieller's theorem. As supplementary analyses the incremental cost per extra person with a clinically significant improvement in function, and per extra person perceived to be recovered will be calculated

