Several functional tests will be included. The stair climb test [26] involves timing how long it takes participants to ascend and descend six steps at their own pace. For the 30 second sit-to-stand test, the number of times participants can rise to a full standing position from sitting and return to sitting in 30 seconds is counted [27]. Walking performance will be assessed by calculating walking velocity (m/sec) as participants walk 20 meters with the instructions 'walk as quickly as you can without overexerting yourself' [28]. Dynamic standing balance will be assessed by the step test [29] and the 4-square step test [30].

In a subset of participants, gait analysis will be performed at baseline and at 13 weeks. Kinematic and ground reaction force data will be recorded simultaneously for five walking trials in usual footwear at self-selected pace using a 3-D motion analysis system with12 cameras (Vicon MX, Oxford, UK) and three force plates (AMTI, Massachusetts, USA) concealed in the floor. Kinematics will be derived from the standard Davis-Kadaba marker set using Vicon Plug-in Gait model. Data will be combined using inverse dynamics to yield measures of external joint moments. The main measures will be peak external hip adduction and abduction moments, peak external hip flexion and extension moments, pelvic drop/rise in the frontal plane and pelvic rotation ranges of motion, and peak and total range of hip motion in the sagittal and transverse planes. Reliability in our laboratory is good for the measures we have subjected to reliability testing, with ICCs of 0.56 to 0.95 (the majority > 0.80) from six patients with hip OA and six controls tested twice one week apart.

The Assessment of Quality of Life instrument version 2 (AQoL II) has 20 questions that cover six dimensions of health-related quality of life including independent living, social relationships, physical senses, coping, pain and psychological wellbeing. The AQoL has strong psychometric properties and is more responsive than other widely-used scales [31,32]. It produces a single utility index that ranges from -0.04 (worst possible health-related quality of life) to 1.00 (full health-related quality of life). A clinically important difference in health-related quality of life can be defined as a change of 0.04 AQoL units [33]. The AQoL will be collected at weeks 0, 13, and 36.

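### As worded, the QALY rule weights AQoL changes by 13 and 36 weeks instead of the 18 and 11.5 weeks of an area under the curve; followed literally, it would give a wrong QALY difference

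*Protocol article*

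**What the plan says.** The Economic evaluation section makes cost per QALY the primary economic analysis and sets the horizon: "QALYs will be calculated using the AQoL scores over 36 weeks". It then gives the construction: "Differences in mean change from baseline for the AQoL to each time point will be weighted by the time from baseline", using regression models "adjusting for baseline levels of the AQoL to construct QALYs, and then compared between groups". The result enters the main economic ratio: "Incremental cost per QALY will be calculated as the ratio of the difference in mean cost to the difference in mean QALYs".

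The visit times are fixed under Secondary outcome measures: "The AQoL will be collected at weeks 0, 13, and 36". The article gives no formula and no numerical weights. It mentions neither an area under the curve nor the lengths of the intervals between visits.

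**The concern.** A QALY is utility accumulated over time. Each AQoL measurement should therefore count for the stretch of follow-up that it represents, not for the time elapsed since baseline. Under the stated rule the week-13 change counts for 13 weeks and the week-36 change for 36 weeks. The first 13 weeks are then counted twice, and the final visit receives most of the weight, although it should receive the smaller share.

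At stake is the denominator of the incremental cost per QALY, and with it the test of H4, the secondary hypothesis on cost-effectiveness. An error in the QALY difference passes into the ratio as its inverse.

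**Working it through.** **Inputs.** AQoL at weeks 0, 13 and 36 (Secondary outcome measures). Horizon of 36 weeks and adjustment for baseline AQoL (Economic evaluation). Write D13 and D36 for the baseline-adjusted between-group differences in AQoL change; the difference at week 0 is then 0. To put sizes on the scale I use 0.04, from the statement "A clinically important difference in health-related quality of life can be defined as a change of 0.04 AQoL units". That is an illustration only: the article does not present 0.04 as an expected between-group difference, and the ratios below do not depend on it. The article states no QALY figure, so there is nothing to reproduce first.

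**Area under the curve (trapezoidal rule), in weeks.**
13 × (0 + D13)/2 + 23 × (D13 + D36)/2 = 18 × D13 + 11.5 × D36. The weights total 29.5.

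**Rule as worded, in weeks.**
13 × D13 + 36 × D36. The weights total 49, which is 36 + 13.

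**Share of weight on week 36.** Area under the curve: 11.5/29.5 = 39%. As worded: 36/49 = 73%.

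**Results in QALYs (weeks divided by 52).**

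| Assumed D13, D36 | As worded | Area under the curve | Ratio |
|---|---|---|---|
| 0.04, 0.04 (constant) | 0.0377 | 0.0227 | 49/29.5 = 1.66 |
| 0.04, 0.02 (halved) | 0.0238 | 0.0183 | 31/23.75 = 1.31 |
| 0.04, 0 (gone) | 0.0100 | 0.0138 | 13/18 = 0.72 |
| 0, 0.04 (late only) | 0.0277 | 0.0088 | 36/11.5 = 3.13 |
| 0.04, −0.02 (reversed) | −0.0038 | +0.0094 | sign changes |

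For the same cost difference, a constant effect makes the cost per QALY 29.5/49 = 0.60 of its proper value, about 40% too low. An effect gone by week 36 makes it 18/13 = 1.38 times its proper value, about 38% too high.

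**When the two rules agree.** 13 × D13 + 36 × D36 = 18 × D13 + 11.5 × D36 gives 24.5 × D36 = 5 × D13, so D36 = 0.204 × D13. For any other pattern they differ.

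**Charitable variants.**
- Weights of 13 and 36 rescaled to total 36 weeks: ratios to the area under the curve of 1.22 (constant), 0.96 (halved) and 0.53 (gone).
- Weights equal to the interval lengths, 13 and 23 weeks: 36/29.5 = 1.22 (constant), 24.5/23.75 = 1.03 (halved) and 13/18 = 0.72 (gone).

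Neither reproduces the area under the curve in general.

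**The case against.** The strongest objection is that the phrase may simply be compressed wording for time-weighting in a condensed article. Its stated purpose is to construct QALYs, and the sentence before it sets a 36-week horizon that weights totalling 49 weeks would contradict. An article may also leave a full formula to the analysis plan. Much of this stands: the intention may well have been an area under the curve, and the lack of a formula is not a fault. What remains is that the article does state a rule, and its words do not describe the weights of 18 and 11.5 weeks. If an area under the curve was meant, the sentence misstates it.

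Three stronger inferences are tempting but not supported.

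- *That the economic result is wrong.* The article reports no economic result and never writes 13 and 36 as weights. The error arises only if the sentence is followed literally, and its size and direction depend on a trajectory that the article does not give.
- *That no proper standard error is available, because QALYs are built from group differences rather than per participant.* The text does not exclude individual QALYs. In any case the trapezoidal QALY is linear in the AQoL scores. With complete or imputed data and the same covariates, regressing individual QALYs on group and baseline AQoL gives (18 × D13 + 11.5 × D36)/52, and its standard error follows from the variances and covariance of the two differences.
- *That the rule as worded exceeds an absolute maximum gain.* For a constant 0.04 it gives 0.0377, above 0.04 × 36/52 = 0.0277. That figure is a bound only for a difference of 0.04 throughout, not a general limit.

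**Conclusion.** The concern holds in conditional form. Taken literally, the stated weighting is not an area under the AQoL curve over 36 weeks, and the QALY difference in the primary economic ratio would be wrong unless D36 happened to be about 0.204 × D13. Under the assumed trajectories the error runs from a 66% overstatement (constant difference), through 31% (halved by week 36), to a 28% understatement (gone by week 36). A late-only or reversed effect would distort it further. These figures rest on the literal reading, a zero adjusted difference at baseline, straight-line change between visits and the trajectories shown.

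This should be fixed, but it does not threaten the trial. Cost-effectiveness is a secondary aim. The sample size, the data collection and the pain and function primary outcomes are untouched.

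**What to change.** Replace the weighting phrase in Economic evaluation with wording such as: *QALYs over 36 weeks are the area under the AQoL curve by the trapezoidal rule over weeks 0, 13 and 36, [13(u0 + u13)/2 + 23(u13 + u36)/2]/52, compared between groups by regression adjusting for baseline AQoL.* Here u0, u13 and u36 are the AQoL utilities at the three visits. Use that difference and its standard error in the cost-per-QALY ratio and its confidence interval.

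The cost is one sentence, recorded as a documented clarification of the analysis. The AQoL is already collected at every visit needed.

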### Timelines

Ethics approval was obtained from the Human Research Ethics Committee of the University of Melbourne in April 2010. Recruitment and training of the physiotherapists was undertaken in April 2010 and recruitment of participants has commenced. All participants are expected to have completed the study by September 2012.

## Discussion

There are several major strengths of the intervention design in this study. Firstly, the multimodal nature of the active physiotherapy program mimics contemporary physiotherapy clinical practice in Australia and many other countries. Patients are treated with a combination of manual therapy techniques and complementary exercises. Given that both exercise and manual therapy alone have been shown to be effective for symptomatic relief in hip OA [8], we contend that the multimodal nature of our program is likely to be more efficacious than either intervention alone.

Secondly, patients' treatment programs are individualised using a problem-solving approach following assessment of musculoskeletal impairments. This allows the program to target the presenting musculoskeletal impairments that contribute the patients' symptoms and functional limitations. It also aligns with the guidelines from EULAR, which recommend tailored treatment [4]. The semi-structured nature of the program, where there are constraints on the number and options for manual therapy techniques and exercises from which the physiotherapists can choose, will reduce treatment variation and allow the delivered treatments to be more easily reported and replicated. Finally, the delivery of the interventions by multiple practicing community physiotherapists will improve the generalisability of the findings.

We considered it important to control for non-specific treatment effects (often referred to as placebo effects) in the study design, given the role these play in influencing treatment outcome. A recent meta-analysis showed that for active treatment of chronic pain conditions (not specifically hip OA), spontaneous recovery contributes around 10% and placebo effects around 30% [50]. Placebo effects have also been found to be greatest for non-pharmacological interventions and for patient-reported outcomes particularly pain [51]. In fact, the sham physiotherapy treatment that we will utilise was associated with a 38% reduction in pain in our previous study in patients with knee OA [15]. While we acknowledge that such indirect treatment effects are an important component of a physiotherapy treatment, we wish to evaluate the additional benefit of direct treatment that target identified musculoskeletal impairments. We did not include a 'no treatment' option as a third study arm as natural recovery is unlikely to occur in these participants who have at least a mild degree of radiographic joint change and report functional disability at baseline.

Our outcome measures are those recommended for use in clinical trials of OA [20]. These include self-report measures of pain, function, quality of life and global response to treatment. A range of other measures are included to also incorporate functional performance, strength, range of motion, psychological aspects, gait biomechanics and physical activity levels in our investigation. We have specified two primary outcomes with the other measures being either secondary outcomes or mechanistic measures which will help us understand the underlying mechanisms explaining changes in pain and function. A health economics assessment is included given the need to justify the cost-effectiveness of treatments in the current economic climate.

## Conclusions

This study uses a randomised controlled trial design to investigate whether a multimodal individualised physiotherapy program that incorporates manual therapy and exercise is more efficacious and cost-effective for the management of symptoms in people with hip OA than a sham physiotherapy treatment that controls for therapist attention. The study design leads to some limitations of generalisability due to a number of inclusion/exclusion criteria, however the design has major strengths related to reproducibility and reflecting contemporary clinical practice. The findings will enable evidence-based recommendations as to the usefulness of this conservative option for the management of patients with hip OA.
